# Does caffeine reduce postoperative bowel paralysis after elective laparoscopic colectomy? (CaCo trial): study protocol for a randomized controlled trial

**DOI:** 10.1186/s13063-016-1297-1

**Published:** 2016-04-04

**Keywords:** Colon surgery, Postoperative bowel paralysis, Caffeine, Postoperative management, Laparoscopic colectomy, Ileus

## Abstract

**Background:**

Postoperative bowel paralysis is common after abdominal operations, including colectomy. As a result, hospitalization may be prolonged, thereby leading to increased cost. A recent randomized controlled trial showed that the consumption of regular black coffee after colectomy is associated with a significantly faster resumption of intestinal motility. The mechanism by which coffee stimulates intestinal motility is unknown, but caffeine seems to be the most likely stimulating agent. Thus, the effect of caffeine on postoperative bowel activity after colon surgery will be analyzed in this trial, herein referred to as CaCo.

**Methods/design:**

Patients scheduled for elective laparoscopic colectomy or upper rectum resection are eligible to participate in this double-blinded, placebo-controlled, randomized trial. Patients fulfilling all inclusion criteria will be allocated after the surgical procedure to one of three treatment arms: 100 mg caffeine, 200 mg caffeine, or placebo (corn starch). Patients will take the capsules containing the study medication three times daily with a meal. The primary endpoint of the study is the time to a solid bowel movement. The study treatment will be stopped after the patient produces a solid bowel movement or has taken ten capsules, whichever occurs first. To determine the colonic passage time, patients will take a capsule with radiopaque markers at breakfast for the first 3 days after surgery. On the fourth day, the location of the markers will be determined with an abdominal X-ray scan. Further secondary objectives are the postoperative morbidity and mortality, well-being, sleeping behavior, and length of hospital stay.

The study size was calculated to be 180 patients with an interim analysis occurring after 60 patients.

**Discussion:**

From a previous study investigating coffee, evidence exists that caffeine might have a positive influence on the postoperative bowel activity. This double-blinded, placebo-controlled, randomized trial tries to show that caffeine will shorten the postoperative bowel paralysis and, thus, will improve recovery and shorten the hospital stay after colon surgery.

**Trial registration:**

Clinicaltrials.gov NCT02510911

Swiss National Clinical Trials Portal SNCTP000001131

**Electronic supplementary material:**

The online version of this article (doi:10.1186/s13063-016-1297-1) contains supplementary material, which is available to authorized users.

## Background

Postoperative bowel paralysis is common after abdominal operations, including colectomy [1]. In most patients, after colon resection, normal intestinal function returns slowly. Surgical stress, pain, and bowel paralysis contribute to this delay. A delay in bowel function (ileus) may lead to a prolonged hospital stay, hospital-acquired infections or complications, and pulmonary compromise [1]. Patients with postoperative bowel paralysis have symptoms of pain, distention, and emesis. They may require treatments such as nasogastric tube, decompression, analgesia, fluid, and electrolyte replacement. Consequentially, hospitalization may be prolonged, thereby leading to increased costs.

Because of the significant implications of bowel paralysis after colectomy, surgeons have developed various strategies to minimize postoperative bowel paralysis.

Multimodal approaches to treat postoperative bowel paralysis in colorectal surgery include early feeding; the restricted use of nasogastric tubes; thoracic epidural analgesia; nonspecific pharmacologic agents, such as water-soluble contrast agents (gastrografin); specific agents, such as alvimopan; and a selective μ-receptor opioid antagonist [1–5].

Chewing gum is another approach to stimulate bowel function after surgery [6]. Asao et al. found an earlier return of bowel function and a trend toward earlier hospital discharge in patients who chewed gum after laparoscopic colectomy. Gum is postulated to activate the cephalic-vagal reflex, which is usually enhanced by food, and to increase the production of the gastrointestinal hormones associated with bowel motility [6].

Coffee is a popular beverage with well-known effects on general well-being, the central nervous system, and the cardiovascular system [7], but information is limited regarding its effects on gastrointestinal function. The gastrointestinal system can be stimulated by food with a substantial caloric content, acidity, osmolality, or volume load. Brewed and filtered coffee is hypotonic, as is water, which serves as a control in most studies investigating coffee. The hypotonicity of coffee, therefore, is unlikely to be responsible for the effects on the gastrointestinal tract. More likely, the ingredients of coffee have a pharmacological effect on the gut.

Twenty-nine percent of a group of volunteers who answered a questionnaire concerning their bowel habits claimed that coffee induced a desire to defecate [8]. Rectosigmoid motor responses to coffee were investigated with a multiport manometry in these volunteers who claimed that coffee caused a desire to defecate and in volunteers who did not so claim. An increase in colonic motor activity was found after 4 min of ingestion of both regular and decaffeinated coffee in the responders but not in the nonresponders. After water, no response in any volunteer was found. Rao et al. performed an ambulatory manometry with a catheter positioned from the rectum up to the midtransverse colon [9]. They studied the effects of 240 ml of regular coffee, decaffeinated coffee, water, and a 1000-kcal meal on colonic motility. Regular coffee, decaffeinated coffee, and the meal induced more colonic activity and more propagated contractions than water. Caffeinated coffee was concluded to stimulate colonic motor activity at a magnitude comparable to a high-calorie meal, 60 % stronger than water, and 25 % stronger than decaffeinated coffee.

A recently performed randomized controlled trial at the University of Heidelberg showed that the consumption of regular black coffee after colectomy is safe and is associated with a significantly faster resumption of intestinal motility [10]. Neither previous studies nor the study from Heidelberg could clearly explain the mechanisms by which coffee stimulates intestinal motility. The most obvious stimulating agent would be caffeine. Therefore, we would like to investigate the role of caffeine on bowel motor activity in this study.

This study is restricted to laparoscopic colectomies because colectomies are increasingly performed by this access technique (our institution: 50–60 % of all colectomies in 2014, German speaking countries: 25–30 %). Since the time to bowel movement is significantly longer after open surgery, open and laparoscopic approaches cannot be compared without significant bias.

## Methods/design

### Study objectives

With this study, we would like to address whether caffeine has a beneficial effect on bowel paralysis after colon resections and whether the side effects of caffeine are within a tolerable range. If we can prove our assumption, caffeine would be a very cost-effective drug to treat postoperative bowel paralysis and could help to shorten the length of the hospitalization.

### Study design

This trial is a double-blinded, placebo-controlled, randomized trial with three arms. Patients will be randomized after the surgical procedure to receive either 3 × 100 mg caffeine, 3 × 200 mg caffeine, or 3 × 250 mg corn starch (placebo) daily. Study participants will be equally allocated to the three arms (1:1:1). The study is an investigator-initiated trial, and the principal investigator also acts as the sponsor. The study will be performed at two sites (St. Gallen and Rorschach) of a major, nonacademic, Swiss medical center. Both sites belong to the same department of surgery.

The study protocol was drafted following the SPIRIT statement (see Additional file 1 for a detailed SPIRIT checklist).

### Outcomes

The primary outcome of the study will be the return to normal bowel function after colon resection. The primary endpoint will be the time to the first bowel movement after surgery. Secondary objectives are the safety of the caffeine treatment, particularly the degree and perception of the known effects of caffeine, such as agitation and insomnia, and the recovery from surgery, morbidity, and mortality.

### Study population

Study participants will be recruited from patients of the Department of General, Visceral, Endocrine and Transplantation Surgery scheduled for laparoscopic elective colon and upper rectum resection. The indication for surgery (oncologic or nononcologic) is not a selection criterion.

In particular, the patient has to fulfill the following criteria to be considered for study inclusion:The patient is scheduled for elective laparoscopic colectomy (right or left hemicolectomy, segmental resection, extended hemicolectomy, sigmoid resection, or upper rectum (anastomosis higher than 7 cm above the anal verge)).The patient’s age is equal to or over 18 years old. As long as the patient is fit for surgery, no upper age limit exists.The patient gives informed consent before surgery.

The following criteria will exclude the patients from trial participation:Participation in another concurrent interventional trialNeed for a stoma (colostomy or ileostomy) or reversal of a stoma, if the patient had complete bowel obstructionKnown hypersensitivity or allergy to caffeine/coffeeExpected lack of compliance (patient is notorious for not following medical instructions, like taking medications as prescribed, or following necessary diets)American Society of Anesthesiologists (ASA) Physical Status Score of IV or VImpaired mental state or language problemsAlcoholism or drug abusePrevious extensive abdominal surgery (any open or laparoscopic abdominal surgery except laparoscopic appendectomy, cholecystectomy, or hernia repair)Inflammatory bowel diseaseClinically significant cardiac arrhythmia (patient suffers from physical complaints or is on regular medication)Cardiac insufficiency (like the previous criterion as safe guard against the effects of caffeine)Pregnancy, lactation, or childbearing potential without using adequate contraceptionIntake of opioid analgesics, or steroids > 5 mg/day for ≥ 7 days before surgeryUnder antidepressive medicationLiver cirrhosis or compromised liver function (MELD score > 15) (Caffeine is metabolized in liver cells, and impaired liver function would result in a prolonged half-life of the caffeine.)

The final decision to include (i.e., to randomize) the patient in the trial will be made at the end of the surgery. The following criteria have to be fulfilled:No major change of the planned surgery (like conversion to open, unplanned placement of a stoma, additional resections of adjacent organs, or other major unplanned procedures)No epidural anesthesia used during or after surgery

### Study withdrawal and stopping medication

After randomization, the patients can withdraw at any time if they own wish without giving any reason.

Study treatment will be stopped for the following reasons:Any adverse event resulting from surgery that might interfere with the study drug or might lead to meaningless endpoint data (e.g., organ failure, anastomotic failure, or postoperative dementia). Due to the complexities of postoperative morbidity, no list of fixed criteria will be established. If such an event occurs before the first study medication will be taken, the patient will be withdrawn from the study and replaced by another patient.Serious adverse events occur that are definitively or probably related to the study drug.Tachycardia, defined as a pulse of over 120/min three times within 1 hour, occurs.In the investigator’s opinion, continuation of the treatment is detrimental to the patient’s well-being.

Unless the patient wishes to withdraw from the study, all scheduled examinations will be performed as planned as long as they are meaningful and do not pose an unnecessary burden to the patient (e.g., no X-ray examination will be performed if treatment is stopped very early or if the patient has multiple vomiting events during the first 3 days postoperatively). Thus, stopping the medication does not automatically constitute withdrawal from the study.

The investigator can withdraw a study patient if a reoperation before the return to normal bowel function is required, an epidural analgesia was placed, if there are signs of renal insufficiency or an acute renal insufficiency, or if the patient clearly is not compliant (repeated refusal to take study medication or is consuming caffeine-containing beverages or food).

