**Fig. 1 Fig1:**
[figure not shown]
Time course of the study treatment. Study treatment starts the evening of surgery if wound dressing was applied before 1 p.m.; otherwise, in the morning of the next day. Study treatment continues until the first solid bowel movement or until ten capsules have been taken (whichever occurs first). The *dotted line* at both ends of the study treatment period indicates that the start and end of the study treatment can vary according to the above-stated rules

If the wound dressing was placed before 1 p.m., the first capsule will be given in the evening; otherwise, in the morning of the following day. Patients will take a total of ten capsules, one with each meal (three times daily). However, the medication will be stopped after the primary endpoint (normal bowel movement) has been reached. The remaining capsules will be returned to the study center. A placard will be attached to the patient bed to indicate study participation and that the patient is not allowed to consume caffeine-containing beverages or food.

In addition to the study treatment, the patients will take a capsule with radiopaque markers every morning starting with the day after surgery for 3 days. On day 4 after surgery, a patient will undergo X-ray imaging to determine the location of the markers to determine the colonic passage time.

Otherwise, the treatment will not differ from the treatment of the colectomy received outside of the study, including the treatment of an ileus after the end of the study period. In case of an ileus after the patient has taken the last study medication, the underlying medical conditions will be corrected, in particular, electrolyte or acid-base abnormalities. Patients suffering from vomiting or distention will receive a nasogastric tube. Finally, patients with an ileus will receive laxatives (magnesium salts, Laxoberon, and one enema/day) and prokinetic drugs (erythromycin 3 × 100 mg/day i.v. for 3 days, and 12–24 h later, metoclopramide 10–30 mg/day iv, together with neostigmine 0.5–1.5 mg iv).

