### Statistical analysis

One interim analysis is planned to assess the primary outcome and the safety of the treatment after 60 patients have been randomized. The statistician will provide an analysis of the primary outcome and a summary of adverse events (in particular, adverse events attributable to caffeine). In this analysis, the arm assignments will not be revealed (blinded); the arms are only labeled A, B, and C. The results will be presented to the data and safety monitoring committee (DSMC). Based on these data, the trial chairperson and the DSMC will decide whether to continue the trial without modification, continue the trial with modification, or stop the trial due to safety or efficacy concerns. If in doubt, the DSMC can ask to reveal the arm assignments before making a final decision. Early stopping of the trial for efficacy at the interim analysis should only be instituted if the benefit of the treatment is shown “beyond reasonable doubt.” A nominal p-value < 0.0007 (O’Brien Fleming alpha spending, see below) provides guidance in this instance but is not binding for this decision. No formal criteria for early stopping for safety reasons will be instituted. The DSMC will make this decision based on statistical analysis, as well as on clinical judgment.

The results of the interim analysis will be confidential and strictly limited to the trial statistician and the trial chair and co-chairs, as well as the DSMC. This confidentiality should prevent any bias by the interim results on the continuation of the trial.

Statistical analysis will be performed with a current R environment (www.r-project.org). For baseline characteristics, descriptive statistics will be used as appropriate. All confirmatory analyses will primarily be performed as an intention-to-treat-analysis, assessing all patients with available data for the outcomes according to the randomization. The significance level alpha for analysis of the primary outcome will be adjusted to the exact proportion of information included in the interim analysis if the analysis is not performed at exactly 60 enrolled patients. For all other analyses, two-sided significance tests with an alpha of 0.05 will be applied.

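### Waiving the day-4 film after repeated vomiting makes colonic passage time missing because of a symptom of bowel paralysis, and the early-stop waiver does not say which stops it covers

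*Protocol article*

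**What the plan says.** All places are in the Protocol article.

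- **Study withdrawal and stopping medication.** After treatment is stopped, "all scheduled examinations will be performed as planned as long as they are meaningful and do not pose an unnecessary burden to the patient". The example given is that "no X-ray examination will be performed if treatment is stopped very early or if the patient has multiple vomiting events during the first 3 days". Neither the vomiting count nor the meaning of a very early stop is defined. The stopping reasons listed just before are surgical events ("Any adverse event resulting from surgery that might interfere with the study drug or might lead to meaningless endpoint data"), serious adverse events related to the drug, a pulse criterion ("Tachycardia, defined as a pulse of over 120/min three times within 1 hour, occurs") and the investigator's opinion.
- **Abstract and Study outline.** Treatment also ends by design at the primary endpoint: "The study treatment will be stopped after the patient produces a solid bowel movement or has taken ten capsules, whichever occurs first", and again "the medication will be stopped after the primary endpoint (normal bowel movement) has been reached".
- **Endpoints and Study outline.** Marker capsules are taken on days 1 to 3 and one film on day 4, with no exception for an early bowel movement. Passage time is the number of markers in the colon times 2.4 h. Vomiting events are an outcome in their own right.
- **Background.** "Patients with postoperative bowel paralysis have symptoms of pain, distention, and emesis".
- **Statistical analysis.** The intention-to-treat analysis is described as "assessing all patients with available data for the outcomes according to the randomization". Secondary continuous outcomes are analysed by regression of mean ranks on dose, with transit time also stratified by gender.

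**The concern.** Whether a patient has a value for colonic passage time depends partly on what happens after randomization. Repeated vomiting is both a trigger for omitting the film and, by the protocol's own account, a sign of the condition under treatment. If caffeine shortens paralysis, more placebo than caffeine patients would vomit and lose their film, and those lost would tend to be slow. An available-data comparison then leaves out part of the slow end, unequally by arm.

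The early-stop waiver raises two further questions. Safety stops such as tachycardia may be more common on caffeine, so even the narrow reading can make missing films differ by arm. And because capsules also stop at the bowel movement, site staff could apply the waiver to a patient who has recovered quickly and for whom a further film looks unnecessary.

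At stake is the trial's imaging-based measure of motility. The bowel-movement and flatus endpoints rest on questioning the patient and on nursing records.

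**Working it through.** **1. The plan's own figure.** The sample size concerns the primary endpoint. With a 10 h difference, SD 20 h, two-sided alpha 0.05, power 80 % and 1:2 allocation, the placebo n is (1 + 1/2) × (1.960 + 0.842)² × (20/10)² = 47.1, rounded up to 48, with 96 on caffeine. The total is 144, and 144/0.8 = 180. Both stated figures reproduce, and the film waiver does not touch them. The protocol gives no figure for passage time or for omitted films, so what follows is illustration.

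**2. Ceiling of the measure.** Three capsules of ten markers give at most 30 × 2.4 = 72 h.

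**3. Assumptions (not in the documents unless stated).** Underlying passage time is normal, mean 62 h on placebo and 52 h on caffeine, SD 20 h. The 10 h and 20 h are borrowed from the sample size section, where they refer to time to bowel movement; the means are invented. Half of patients above 80 h vomit repeatedly. Where the early-stop waiver is applied to bowel-movement stops, it removes values below 33 h. Observed values are capped at 72 h.

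**4. All films taken.** The capped mean is 72 − 20 × [zΦ(z) + φ(z)], with z = (72 − mean)/20.
- Placebo, z = 0.5: 72 − 20 × 0.6978 = 58.04 h
- Caffeine, z = 1.0: 72 − 20 × 1.0833 = 50.33 h
- Difference 7.7 h

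**5. Vomiting waiver only.** Share above 80 h: 18.4 % placebo, 8.1 % caffeine. Half lose the film: 9.2 % and 4.0 %, all sitting at 72 h.
- Placebo: (58.04 − 0.0920 × 72)/0.9080 = 56.62 h
- Caffeine: (50.33 − 0.0404 × 72)/0.9596 = 49.42 h
- Difference 7.2 h, a loss of about 0.5 h or 6 to 7 %

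**6. Bowel-movement stops before 33 h waived as well.** Share below 33 h: 7.35 % placebo, 17.1 % caffeine. Their contribution to the mean is mean × Φ(a) − 20 × φ(a), with a = (33 − mean)/20: 1.77 h and 3.81 h.
- Placebo: (58.04 − 6.63 − 1.77)/0.8344 = 59.5 h
- Caffeine: (50.33 − 2.91 − 3.81)/0.7886 = 55.3 h
- Difference about 4.2 h

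A simulation with 4 million values per arm gave 7.70, 7.20 and 4.19 h.

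**7. Dependence on the link between vomiting and transit.** In a separate simulation without the cap and with a true difference of 0.50 SD, waiving 5 to 20 % of patients by a marker correlated 0.5 to 1.0 with passage time left 0.47 to 0.28 SD. At correlation 0.8 with 10 % waived, 15.0 % of placebo and 7.5 % of caffeine films were lost, and Mann-Whitney power with 48 and 96 patients fell from about 78 % to 64 %. Without the cap, losses come out larger than the measure allows.

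**8. Direction.** As a deliberate extreme, let the vomiting waiver act on slow caffeine patients as in step 5 but on no placebo patient. The difference becomes 58.04 − 49.42 = 8.6 h, above 7.7 h. Attenuation is likely if caffeine works, not certain.

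**The case against.** **A reader might infer that the plan withholds films from both the fastest and the slowest patients.** The documents do not support the first half as a rule. The early-stop phrase follows a list of safety and morbidity reasons on which a bowel movement does not appear. The Study outline mentions the stop at the bowel movement and then schedules the markers and the day-4 film without exception, as does the Endpoints section. The well-being questionnaire on day 4 is described as falling after treatment, so assessments are plainly meant to outlast the capsules. This stands: the fast-end loss is a possible misreading that the wording leaves open, and the 4.2 h figure applies only under it.

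**The vomiting waiver has a measurement reason.** The formula counts only markers in the colon. Markers vomited or held in the stomach lower the count and could make a slow patient look fast. This stands too, and is why no film should be forced in these patients. It does not justify leaving them out of every comparison.

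**Vomiting is a symptom, not a measure of paralysis, and the bias may run the other way.** The Patient safety section lists gastrointestinal complaints and tachycardia among caffeine's effects. Waivers could be more frequent on caffeine, and a worst rank would then count against it. This stands and limits what can be said about direction.

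**Handling of missing values may belong in an analysis plan not shown.** True of the rank analysis. But the waiver itself and the available-data rule are stated in the protocol, so the selection follows from what is written.

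**Conclusion.** The point holds for the vomiting waiver. Applied as written with an available-data analysis, it makes a secondary outcome missing because of a post-randomization event that the protocol ties to bowel paralysis. For the early-stop waiver, what holds is an ambiguity: the text does not separate premature safety stops from planned completion at the bowel movement. The stronger claim, that the fastest patients are set to lose their films, is not established.

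On the reading that the text best supports, the loss is modest: about 0.5 h of an assumed 7.7 h. Under the literal wide reading it is about 3.5 h (7.7 to 4.2 h). Both rest on assumed means, an assumed vomiting rate and an assumed 33 h cut-off, and on passage time tracking time to stool. They are mean differences, whereas the plan uses mean ranks. Attenuation is the likelier direction if caffeine works, but it is not guaranteed. The primary endpoint and the sample size are unaffected.

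**What to change.** - In the section on study withdrawal and stopping medication, state that ending the capsules because of a bowel movement does not waive the day-4 film, and say what counts as a very early stop and as multiple vomiting events.
- In the analysis of colonic passage time, show the films-only result side by side with a mean-rank analysis that places patients whose film was omitted for repeated vomiting at the longest-passage rank.
- Report omitted films by arm and by reason (vomiting, safety stop, other).

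The cost is one clause in the protocol, one sentence in the analysis and one small table. No procedure is added beyond the film already planned. The downside is that vomiting from other causes, including caffeine itself, also receives the worst rank. Neither analysis should therefore stand alone; agreement between them would be reassuring, and disagreement would show how far the conclusion rests on the omitted films.
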